### Strategies to improve adherence to interventions {11c}

During the follow-up period, investigators will be arranged to respond to patient inquiries. Investigators will contact patients 2 (± 1) days before each visit to improve adherence to intervention protocols.

### Relevant concomitant care permitted or prohibited during the trial {11d}

Not Applicable. No relevant concomitant care is prohibited during the trial.

### Provisions for post-trial care {30}

Follow-up visits at the outpatient clinic will be arranged and patients will receive post-trial treatment plans. If patients suffer harm from trial participation. compensation will be made by Beijing Hospital in accordance with relevant laws and regulations.

### Outcomes {12}

Assessment protocol for the current study from V1 to V14 is provided in Fig. 2.

#### Primary outcome measure

BCVA: Best corrected visual acuity is measured using standard ETDRS protocol at baseline and every follow-up visit. Changes in visual acuity will be compared between the two groups at a 12-month follow-up.

#### Secondary outcome measures

CMT: OCT is used to measure CMT at baseline and every follow-up visit. Changes of CMT will be compared between the two groups at 12-month follow-up.

Number of injections: Number of intravitreal injections of two groups will be compared at a 12-month follow-up.

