### Objectives {7}

The purpose of this study is to evaluate the safety and efficacy of micropulse laser combined with intravitreal ranibizumab injections in the treatment of DME. Study subjects are 72 patients (more patients may be recruited) diagnosed with diabetic macular edema. By using a prospective randomized double-blind controlled study method, we hope to compare the changes of visual acuity and macular edema regression between micropulse laser combined with ranibizumab group with ranibizumab monotherapy group to determine whether the efficacy of micropulse laser combined treatment group in the treatment of DME is not lower than ranibizumab monotherapy and whether these two therapies are equally effective. Our goal is to reduce the number of intraocular injections and establish a new technique for the treatment of DME.

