#### Screening period: from day −14 to day −1

At screening (visit 1, between day −14 and day −1), after signing the informed consent (the model consent form is attached as a supplementary file), the patient is enrolled in the study and will undergo a series of examinations including ETDRS (Early Treatment Diabetic Retinopathy Study) visual acuity test, intraocular pressure measurement, slit-lamp, and indirect ophthalmoscopy, optical coherence tomography (OCT), optical coherence tomography angiography (OCTA), fundus fluorescein angiography (FFA), fundus color photography, vital signs, hematology, urinalysis, blood biochemistry, and glycosylated hemoglobin to assess eligibility for the study.

#### Treatment period: from day 1 to month 11

At baseline (visit 2, day 1), eligible patients will be randomized by 1:1 ratio into micropulse laser combined with ranibizumab group or ranibizumab monotherapy group. After baseline visit, all patients receive 3 consecutive monthly ranibizumab injections. Subjects will then return to the study site on day 90 (± 7 days) and according to the retreatment criteria, patients will either receive micropulse laser and sham intravitreal ranibizumab or sham micropulse laser and intravitreal ranibizumab. Thereafter, subjects will return to the study site every 30 days (± 7 days) for assessment (schedule shown in Fig. 2) and accept appropriate treatment according to the retreatment criteria.

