**Fig. 2 Fig2:**
[figure not shown]
Assessment protocol from V1 to V14. *BSL *Base line, *EOT *End of treatment, *EOS *End of study. (X): Give treatment as needed. b: Except at the time of screening, at month 6 and at month 12 / end of the study, if the investigator needed information to evaluate the retreatment. These assessments are optional for therapeutic needs. c: Evaluation of both eyes. d: At 2 (±1) days after each study treatment, the investigator should contact the patient for a possible report of adverse events

Group I (micropulse laser combined with ranibizumab group): 3 consecutive injections of intravitreal ranibizumab, followed by monthly observation, if:A.Visual acuity decreases by greater than or equal to 5 ETDRS letters due to macular edema, then treat with micropulse laser therapy and sham intravitreal ranibizumab injection.B.Visual acuity stays stable for at least two consecutive treatments (3 consecutive changes of no more than 5 letters), discontinue micropulse laser treatment.

Group II (ranibizumab monotherapy group): 3 consecutive injections of intravitreal ranibizumab, followed by monthly observation. According to the investigator’s judgment, if:A.Visual acuity decreases by greater than or equal to 5 ETDRS letters due to macular edema, then treat with sham micropulse laser and intravitreal ranibizumab injection.B.Visual acuity stays stable for at least two consecutive treatments (3 consecutive changes of no more than 5 letters), discontinue intravitreal ranibizumab injection.

#### Post-treatment follow-up period: from month 11 to month 12

For all patients, the last study assessment will occur at month 12 (1 month after the last possible micropulse laser or intravitreal ranibizumab injection in the study).

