### Intervention description {11a}

Micropulse laser combined with ranibizumab group (group I): After three consecutive intravitreal injections of 0.5mg ranibizumab, patients are followed-up monthly in Beijing Hospital. If visual acuity decreases by greater than or equal to 5 ETDRS letters due to macular edema, then treat with micropulse laser (the treatment parameters we apply are 577nm micro-pulse laser, 200μm spot size, 5% duty cycle of 0.2 seconds, 400mW power, 7×7 grid, panmacular treatment) and sham intravitreal ranibizumab injection. And if visual acuity stays stable for at least two consecutive treatments (3 consecutive changes of no more than 5 letters), then discontinue micropulse laser treatment.

Ranibizumab monotherapy group (group II): After three consecutive intravitreal injections of 0.5mg ranibizumab, patients are followed-up monthly in Beijing Hospital. Sham micropulse laser and intravitreal ranibizumab injection will be performed as needed if visual acuity decreases by greater than or equal to 5 letters due to macular edema. If visual acuity stays stable for at least two consecutive treatments (3 consecutive changes of no more than 5 letters), discontinue intravitreal ranibizumab injection, then discontinue intravitreal ranibizumab injection.

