## Assignment of interventions: Blinding

### Who will be blinded {17a}

Investigators responsible for follow-up evaluation, technicians who operate OCT, and data analysts are blinded. When intervention is required, the patient will either receive intravitreal injections plus sham micropulse laser treatment, or micropulse laser plus sham intravitreal injections. Therefore trial participants are blinded throughout the study. Only the investigators qualified for laser treatment and intravitreal injections are unblinded.

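### On protocol, Group I can receive no active injection after loading, so the secondary comparison of injection numbers is set by assignment and cannot show that laser reduces the need for injections

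*Protocol article*

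**What the plan says.** Under Trial design {8}, in the text on the treatment period, "all patients receive 3 consecutive monthly ranibizumab injections". From the day-90 visit, "patients will either receive micropulse laser and sham intravitreal ranibizumab or sham micropulse laser and intravitreal ranibizumab". The group-specific rules that follow agree. When Group I meets the retreatment criterion, the instruction is: "then treat with micropulse laser therapy and sham intravitreal ranibizumab injection". For Group II it is: "then treat with sham micropulse laser and intravitreal ranibizumab injection". Intervention description {11a} repeats the Group I pairing ("and sham intravitreal ranibizumab injection. And if visual acuity stays stable for at least two consecutive treatments"), and so does Who will be blinded {17a} ("or micropulse laser plus sham intravitreal injections").

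The month-12 assessment is placed one month after the last possible treatment, so retreatment can occur at the monthly visits from month 3 to month 11. Sections {11b} and {17b} take a patient with severe vision loss from worsening edema out of the study. Neither describes a return to ranibizumab within it.

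Against this, Secondary outcome measures lists: "Number of intravitreal injections of two groups will be compared at a 12-month follow-up". Objectives {7} says: "Our goal is to reduce the number of intraocular injections".

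**The concern.** A comparison of injection counts says something about the laser only if patients in the laser arm could receive an injection when their edema returned. Under these rules they cannot. A Group I patient who meets the retreatment criterion receives laser and a sham injection, whether the laser works or not. A low count in that arm reflects the allocation rule and not a lower need.

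This matters because fewer injections is the trial's stated goal and its rationale, and the Discussion already asserts that the combination can bring injections down. A very small p-value on this outcome would be read as confirming that assertion, although a laser with no effect would produce it too. After loading, the design actually compares laser as needed with ranibizumab as needed.

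**Working it through.** The plan gives no figure for this outcome. Its sample-size calculation concerns visual acuity, and only the 36 patients per arm are used here.

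**Inputs from the protocol article**
- Loading injections, both arms: 3 (Trial design {8}; Intervention description {11a}).
- Retreatment opportunities: months 3 to 11, so 11 − 3 + 1 = 9 (Trial design {8}).
- Active injections per retreatment: 0 in Group I, 1 in Group II (Trial design {8}; {11a}; {17a}).
- Patients per arm: 36 (Sample size {14}).
- Injections per year in other studies: 7 to 8 (Background and rationale {6a}).

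**Input assumed**
- Probability *q* that the retreatment criterion is met at a visit: 0.05 to 0.50. The document gives no value.

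**Count allowed by the rules.** Let R1 and R2 be the numbers of retreatments per patient in Groups I and II, each between 0 and 9, for patients who complete loading and stay on protocol.
- Group I: 3 + 0 × R1 = 3, with no variation.
- Group II: 3 + 1 × R2, so from 3 to 3 + 9 = 12.
- Difference in means, Group II minus Group I: (3 + mean R2) − 3 = mean R2.

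R1 has dropped out. However often Group I patients need retreatment, the difference is the same and cannot be negative.

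**Size.** The expected difference is 9*q*.

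| *q* (assumed) | 9*q* | Simulated difference | Injection-count test rejects | Retreatment-session test rejects |
|---|---|---|---|---|
| 0.05 | 0.45 | 0.45 | 100% | 3.9% |
| 0.10 | 0.90 | 0.90 | 100% | 4.35% |
| 0.20 | 1.80 | 1.81 | 100% | 4.1% |
| 0.30 | 2.70 | 2.70 | 100% | 5.0% |
| 0.50 | 4.50 | 4.50 | 100% | 4.55% |

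The last three columns come from a simulation of 36 completers per arm with the **same** *q* in both arms and independent visits. It used a Mann-Whitney test at two-sided 0.05 and 2,000 runs per row. With equal need in both arms, the injection count always declares a difference. The count of retreatment sessions (active laser in Group I, active injection in Group II) rejects at about the nominal 5%.

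**With the cited 7 to 8 injections.** The difference would be 7 − 3 = 4 to 8 − 3 = 5, which corresponds to *q* of 4/9 = 0.44 to 5/9 = 0.56.

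**The case against.** The strongest reply is that this is a coherent substitution design. The trial is a non-inferiority trial with visual acuity as primary outcome. Fewer injections is what the intervention consists of, and visual acuity tests whether that is affordable. An ineffective laser should show there. The outcome text says only that the number will be compared; it names no hypothesis, and Objectives {7} speaks of the number of injections, not the need for them. All of this stands as far as it goes. The primary inference is untouched, and the count is a legitimate description of exposure or cost. The reply does not make a between-arm comparison of the count informative about the laser.

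A reader might infer more than the document supports:
- **That the gap is 4 to 5 injections.** That figure borrows 7 to 8 a year from other studies. Group II's number under this protocol's own trigger is not given, and 12 is a theoretical ceiling.
- **That a meaningless ANOVA is planned.** Statistical methods {20a} describes ANOVA or ANCOVA for changes from baseline. A count of injections has no baseline value, so the text does not clearly assign that method to it.
- **That early exit flatters Group I.** A Group I patient who leaves after loading has 3 protocol injections either way, while a Group II patient who leaves has the count cut short, which shrinks the gap. Group I would gain only if injections after exit were left out, and the document does not say whether they are.
- **That no Group I patient can ever have a number other than 3.** Someone who stops during loading can have fewer. Section {11d} prohibits no concomitant care, so off-protocol injections are conceivable, though no visible rule provides them; the figures are not shown. Counting sham injections would make Group I vary, but that would be a count of sessions, which the outcome text does not state.

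**Conclusion.** The point holds for active injections given on protocol, as the visible text states the rules: 3 in Group I for anyone who completes loading, 3 to 12 in Group II. The difference equals Group II's as-needed injections, about 9*q*. Its direction is settled before any patient is treated, and it carries no information on whether laser lowers the need for injections.

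The direction and the lack of information follow from the treatment rules alone. The size rests on the assumed *q*, and the rejection rates also rest on full follow-up and independent visits. The non-inferiority question on visual acuity is not undermined, and the retreatment rules are not criticised here.

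**What to change.** 1. Report the number of active injections per arm descriptively, as exposure under each strategy, with no test and no claim of laser effect.
2. Make the compared secondary outcome the number of retreatment sessions triggered from month 3 to month 11: active laser in Group I, active injection in Group II. Early exit cuts this count short, so allow for time in study, for example as a rate per monthly visit attended. Exit can itself follow severe vision loss, so show exits by arm alongside, and read the result beside visual acuity.
3. Word the conclusion as laser as needed versus ranibizumab as needed, each after three loading injections.
4. Where known, anti-VEGF injections given to the study eye off protocol or after exit, up to month 12, may be listed descriptively. That total is still largely set by assignment and should not serve as a test of laser effect.

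The cost is small. The outcome wording changes and retreatment sessions must be tabulated. Data management {19} names only examples of what is captured, so the sponsor should confirm that sessions are recorded. The trial gives up a nominally significant secondary result. No treatment rule changes. Trial status places the last visit in the future and {17a} keeps the data analysts blinded, so the change could be made without sight of results by arm.

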### Participant timeline {13}

A flow chart of the study design is shown in Fig. 1.Screening period: from day −14 to day −1Treatment period: from day 1 to month 11Post-treatment follow-up period: from month 11 to month 12

### Sample size {14}

Using two-sided test, with αas 0.05, changes of visual acuity as less than 5 letters between two groups, standard deviation as 6.53 (REVEAL study [12] as reference), enrolling 56 cases of subjects can set the power to 90%. Considering drop out, set the lost follow-up rate as 20%, then the final sample size is calculated as 72 subjects, with 36 subjects in micropulse laser combined with ranibizumab group and 36 subjects in the ranibizumab monotherapy group.

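### The sample-size section claims 90% power for 56 subjects, but its own inputs give about 80%

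*Protocol article*

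**What the plan says.** The calculation is in the protocol article, Sample size {14}. Its inputs are:

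- test and level: "Using two-sided test, with αas 0.05";
- difference: "changes of visual acuity as less than 5 letters between two groups";
- variability: "standard deviation as 6.53", taken from a cited ranibizumab study.

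From these it concludes that "enrolling 56 cases of subjects can set the power to 90" per cent. It then allows for drop-out: "set the lost follow-up rate as 20%, then the final sample size is calculated as 72 subjects", that is 36 per arm. The treatment-period text under Trial design {8} fixes equal allocation ("eligible patients will be randomized by 1:1 ratio"), so 56 means 28 per arm. Trial design {8} also calls this a non-inferiority trial, and Outcomes {12} makes the change in best corrected visual acuity at 12 months the primary comparison.

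**The concern.** The section gives everything needed to recompute its power, and the result misses the stated 90% by about ten percentage points. The number that would give 90% with these inputs is close to 72, yet 72 is presented as 56 plus an allowance for loss. If the allowance is used, the trial runs at about 80% power.

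This matters because the primary question is non-inferiority. Readers use the stated power to judge what a failure to show non-inferiority means. If they believe the chance of missing a truly non-inferior treatment was 10% when it was about 20%, they will give such a failure too much weight as evidence against the combined treatment.

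**Working it through.** **Inputs.** Two-sided alpha 0.05, difference 5 letters, SD 6.53 and 56 evaluable subjects (all Sample size {14}); 1:1 allocation (Trial design {8}), so n = 28 per arm.

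**Power at the stated size.**

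- Standard error of the difference = SD × √(2/n) = 6.53 × √(2/28) = 1.745 letters.
- Standardised difference = 5 / 1.745 = 2.865.
- Normal approximation: Φ(2.865 − 1.960) = Φ(0.905) = **81.7%**.
- Noncentral t with 54 degrees of freedom: **80.3%**.

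The stated 90% does not reproduce.

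**Size needed.** n per arm = 2 × (z for alpha + z for power)² × SD² / difference².

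- 80% power: 2 × (1.960 + 0.842)² × 6.53² / 5² = 26.8, so 27 per arm (54 in total). The t-test needs 28 per arm (56), since 27 per arm gives 78.8%.
- 90% power: 2 × (1.960 + 1.282)² × 6.53² / 5² = 35.8, so 36 per arm (72). The t-test needs 37 per arm (74).

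So 56 is exactly the t-test answer for 80%. That suggests an 80% calculation labelled as 90%, but does not prove it.

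**Drop-out.** 56 / 0.8 = 70, so 72 is a reasonable inflation of 56; that step is not the fault. Going the other way, 72 × 0.8 = 57.6 evaluable.

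| Analysed (per arm) | Power, t-test | Power, normal |
|---|---|---|
| 56 (28/28) | 80.3% | 81.7% |
| 57 (29/28) | 81.0% | 82.4% |
| 58 (29/29) | 81.7% | 83.0% |
| 72 (36/36) | 89.3% | 90.1% |

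**Other readings.**

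- *Non-inferiority, margin 5, true difference 0, one-sided 0.025.* Sample sizes are the same as above: 27 per arm for 80% and 36 for 90% by the normal approximation. Whether the 5 letters are a margin or a difference to detect makes no difference to the result.
- *One-sided 0.05.* Power at 56 is 88.2% (t) or 88.9% (normal), and 90% needs 60. The section says two-sided.
- *56 per arm.* Power would be 98%, but the total of 72 rules this out.
- *Equivalence within ±5 letters at a true difference of 0*, since Objectives {7} also asks whether the two treatments work equally well. By simulation, power at 56 is 61% with a 95% confidence interval or 77% with a 90% interval, which is further from 90%.
- *A slip in one input.* For 90% by t-test at 28 per arm the SD would have to be 5.67, or the limit 5.76 letters. The protocol gives neither.

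**The case against.** Nobody can defend 90% at 56, but it can fairly be argued that the trial itself may have more than 80% power.

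- *All 72 may be analysed.* The statistical methods section {20a} puts the primary analysis on the full analysis set, and {20c} carries the last post-baseline observation forward. Patients who drop out after a post-baseline visit would stay in, and 72 analysed gives 89.3% to 90.1%. This stands as a possibility. It assumes that carried-forward values have the same SD and the same expected difference as true 12-month values, and it spends the allowance that the section sets aside for loss. The section's own accounting treats lost patients as lost.
- *More patients may be recruited.* Several sections say so, and Trial status reports replacement recruitment. No larger number is fixed, and Sequence generation {16a} allocates exactly 72.
- *Baseline adjustment.* The analysis plans baseline as a covariate. If baseline had a correlation of about 0.5 with the outcome whose SD is 6.53, 28 per arm would give about 90% (residual SD 6.53 × √(1 − 0.25) = 5.66). That correlation is an assumption, and the sample-size section does not use it.
- *The wrong input is unknown.* The misprint could lie in the power, the SD, the sidedness or the number. This stands, and is a reason for the sponsor to check the original calculation before rewording.

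None of these makes the statement about 56 subjects true.

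**Conclusion.** The stated power is wrong as written. On the section's own inputs, 56 evaluable patients give 80% to 82% power, and 72 enrolled with the planned 20% loss give 81% to 83%, depending on the t-test or the normal approximation. The type II error is about 20%, not 10%. Power close to 90% is reached only if all 72 contribute an analysable 12-month value with the SD unchanged.

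The result assumes equal arms, an SD of 6.53 in both, and, if the 5 letters are read as a non-inferiority margin, a true difference of zero. Any true disadvantage of the combined treatment would lower the power further. The type I error and the treatment estimate are not affected.

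**What to change.** The sponsor should check the original calculation for a misprinted input and then restate the paragraph. If the inputs stand, suitable wording is:

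> With a limit of 5 letters, SD 6.53, a true difference of 0 and two-sided alpha 0.05 (one-sided 0.025 for non-inferiority), 56 evaluable patients (28 per arm) give 80% power by t-test. Enrolling 72 with 20% loss leaves 57 to 58 evaluable and gives about 81% to 82%. If all 72 contribute a 12-month value, power is about 89%.

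The 90% claim should go. If the sponsor wants to rely on carried-forward values to count all 72, the paragraph should say so and state that this assumes the same SD and the same expected difference. The words margin, zero true difference and one-sided 0.025 are not in the present section, so the sponsor must confirm that they express what was intended.

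The cost is one corrected paragraph and a less favourable power figure. No added patients and no change to the design or analysis are needed.

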### Recruitment {15}

When physicians meet qualified patients in the outpatient department of ophthalmology, they will refer them to the investigator’s team who are specialized in screening. Sub-investigatiors will then introduce the study to the patients.

## Assignment of interventions: allocation

### Sequence generation {16a}

A table of random numbers will be used for randomizing, Patient number 1 to 72 will each be assigned a random number by using a random number table. Then they are put in numerical order from small to large, the first 36 will be group I (micropulse laser combined with ranibizumab group), and the other 36 will be group II (ranibizumab monotherapy group).

